**Fig. 3 Fig3:**
[figure not shown]
Flow diagram of the study

### The intervention

At the baseline, the intervention includes dental assessment (through visual inspection or dental photography) and the provision of dental advice/recommendation that could include a referral to school dental providers, instructions or oral health promotion (OHP) leaflets, depending on the urgency and severity of the condition. The OHP leaflets are readily available on the Dental Health Services WA website (https://www.dental.wa.gov.au/) and permission has been obtained to use these leaflets.

#### Visual dental examination

A standard dental screening (without radiography) will be performed by registered OHTs (operators) who are blinded to the group allocation of the school. Head-mounted lighting, disposable mirrors and probes will be used to conduct the visual dental screening. Findings from the visual dental assessment will be recorded on an oral health assessment form that follows the guidelines for oral health surveys developed by the WHO [35]. Following the completion of the baseline dental screening, parents of school children allocated to the control group will receive a copy of the screening results based on the visual inspection performed by onsite OHTs. Based on the severity and urgency of dental conditions, children with active caries will be referred to local dental providers for further investigations. Children who are screened caries-free or at low-risk, will not receive active treatment other than OHP leaflets.

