**Methods/design:**

We describe an ongoing parallel, two-armed, non-inferiority randomised controlled trial that compares routine and teledental pathway of dental care in children aged 4–15 years (*n* = 250). Participating schools in Western Australia will be randomly assigned to the control or teledental group, approximately three schools in each group with a maximum of 45 children in each school. All participants will first receive a standard dental examination to identify those who require urgent referrals and then their teeth will be photographed using a smartphone camera. At the baseline, children in the control group will receive screening results and advice on the pathway of dental care based on the visual dental screening while children in the teledental group will receive screening results based on the assessment of dental images. At 9 months follow-up, all participants will undergo a final visual dental screening. The primary outcomes include decay experience and proportion of children become caries active. The secondary outcomes include the diagnostic performance of photographic dental assessment and costs comparison of two pathways of dental care.

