### Allocation

To avoid spill-over effects within a school, we will conduct randomisation using the school as the unit of allocation because the intervention is implemented at the level of the school (Fig. 3). The schools will be randomly allocated in a 1:1 ratio to one of the teledental or control group. For allocation of the participants, a computer-generated list of random numbers will be used. To approximate equality of sample sizes in the study groups, we will use block randomisation with computer-generated randomly permuted blocks of 4 at each school. School-specific randomisation lists are concealed by an independent researcher, and kept in sequence and opened as participants are examined at the baseline and found eligible for enrolment. The research team and data analysts will be blinded to group allocation and will not be aware of the randomisation procedure. Study participants (and their parents/guardians) and OHTs providing the intervention and/or collecting data cannot be blinded to group allocation.

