#### Follow up

At 9 months following the baseline dental assessments, all participants will be invited to undergo a standard visual dental check-up to assess the dental status, determine if treatment was received and see whether parents adhere to the recommendations received at the baseline.

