### Outcome assessment

*Primary outcomes* include decay experience in either dentition as measured by the DFT/dft (decay, filled teeth) index at the baseline and 9-month follow up. Teeth will be classified as carious if have arrested caries, caries into dentine or enamel level caries. In addition to the proportion of children becomes caries-active at the 9-month follow-up which refers to the percentage of children developing one or more new caries in any of the previously caries-free teeth when assessed at the baseline. Data will be collected from one of our system’s functional components running on the backend to automatically record dental assessments based on dental images and through the oral health assessment forms completed by OHTs in the control group.

*Secondary outcomes* include the diagnostic performance of photographic dental assessment versus standard dental examination at the baseline. The participants’ dental care utilisation patterns collected via a baseline survey (Additional file 2) and adapted from Kopycka-Kedzierawski et al. [36]. Also, costs comparison between the two pathways of dental care will be conducted to identify the least costly alternative. The resources for the usual pathway of dental care will include vehicle costs, admin costs (e.g. telephone appointments, printing services and postage) and costs of consumables used in visual dental screening and the dental practitioner’s time. The resources for the teledental pathway of dental care include: software licence fees, ICT equipment, Internet and software engineer’s time, admin costs (e.g. telephone appointments, printing services and postage), costs of consumables used in dental photography, tele-assistants (photographer) time, and offsite dental practitioners’ time for reviewing dental images. Dental care costs for all children include the following: restorations, restorations with crowns and extractions. The costing data will be based on those incurred by the health system and will be derived from a survey and web-based open-access sources [37].

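### The protocol says both that the examining OHTs are blinded and that OHTs collecting data cannot be, and it leaves blinding of the 9-month primary-outcome examination unsettled

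*Protocol article*

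**What the plan says.** Five places in the protocol article bear on this.

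- **Visual dental examination** gives the screening to "registered OHTs (operators) who are blinded to the group allocation of the school" and adds: "Findings from the visual dental assessment will be recorded on an oral health assessment form".
- **Allocation** makes the school the unit of randomisation. It states that participants and parents are unblinded and that "OHTs providing the intervention and/or collecting data cannot be blinded to group allocation". It also says: "The research team and data analysts will be blinded to group allocation".
- **Follow up** says that at 9 months "all participants will be invited to undergo a standard visual dental check-up to assess the dental status". The same visit is to establish whether treatment was received and to "see whether parents adhere to the recommendations received at the baseline". It names neither the examiner nor any blinding.
- **Outcome assessment** defines the first primary outcome by the "DFT/dft (decay, filled teeth) index at the baseline and 9-month follow up". The second is the proportion of children with at least one new carious tooth among those caries-free at baseline. Enamel-level and arrested lesions count as caries.
- **Abstract, Methods/design** confirms that the final assessment is visual in both arms: "At 9 months follow-up, all participants will undergo a final visual dental screening".

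**The concern.** The article gives two opposite answers to one question: does the person scoring the teeth know the school's arm? A team that follows the Allocation section would accept unblinded scoring. A team that follows the Visual dental examination section would keep the examiner unaware.

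The answer matters for these outcomes. Whether an enamel-level or arrested lesion is called present depends on the examiner's threshold. One borderline call in a previously sound tooth is enough to make a child caries-active. Because whole schools are allocated, an examiner who learns a school's arm knows it for every child examined there. A shift in threshold can then act on the whole school, and enrolling more children in that school does not average it out. With about three schools per arm, few other schools would dilute it.

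**Working it through.** **Step 1. Do the two statements concern the same people?** The operators in the Visual dental examination section are OHTs. They examine the child and their findings go onto the assessment form. Outcome assessment names OHT-completed forms as a source of trial data. The operators are therefore OHTs who collect data, and the Allocation sentence covers them. One section says they are blinded and the other says they cannot be.

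**Step 2. Can a narrower reading remove the conflict?** The Allocation sentence might be meant only for OHTs who chart images or give arm-specific advice. Its wording is not limited in that way, because it reaches those who provide the intervention, those who collect data, or both.

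**Step 3. Does the blinding statement extend to 9 months?** It stands under The intervention, and the text around it describes what follows the baseline screening. The 9-month visit is likewise called a standard visual examination, so extending the statement is reasonable. Even then the Allocation sentence would still contradict it.

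**Step 4. Does the design force unblinded examiners?** It does not. According to the Abstract, every child in both arms has a visual examination and photographs at baseline and the same visual examination at 9 months. The procedure itself does not reveal the arm.

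**Step 5. What could a threshold shift do?** No figure in the documents measures this, so the following is illustration only. Let c_T and c_C be the net proportions of children in the teledental and control arms whose caries-active call changes because the examiner knows the arm (added calls minus removed calls). Then

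observed difference = true difference + (c_T − c_C).

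- c_T = 0.01, c_C = 0: the difference moves by +1 percentage point.
- c_T = −0.01, c_C = 0: it moves by −1 point.
- c_T = c_C: the shifts cancel.
- c_T assumed anywhere from 0.01 to 0.05, c_C = 0: it moves by 1 to 5 points.

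For scale, Sample size calculation gives 125 children per arm with 20% drop-out, so 125 × 0.80 = 100 completers. One percent is then one child. If only one of three equal-sized schools in an arm were affected, a net change in 3% of its children would give 3% ÷ 3 = 1% of the arm, again 1 point. If each changed call concerns one tooth, mean DFT/dft in that arm moves by 0.01 teeth for each 1% of children.

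**The case against.** The strongest reply is that this is a loose sentence in a condensed article. The blinding of operators is stated once, the follow-up visit is described in similar terms, and an article need not repeat it. That is fair as far as silence goes: the missing repetition in Follow up would not be a fault on its own. The direct conflict with Allocation remains.

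A second reply is that the route to unblinding is weak, and this largely stands. A child who mentions photographs reveals nothing, since all are photographed. Both arms can receive the same kinds of advice (referral, instructions or leaflets). Follow up does not say that anyone is questioned, and some treatment can be seen in the mouth. A reader might infer that the visit necessarily discloses the arm, but the text does not show that. It shows an enquiry involving unblinded families with no stated order relative to the scoring.

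Third, scoring follows WHO guidelines and an independent researcher audits the OHTs. These measures limit drift in the threshold but do not replace an unaware examiner.

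A reader might also see a conflict between a blinded research team and the mailing of arm-specific results. The article does not say who mails them, and an independent researcher conceals the allocation lists, so that inference is not supported.

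**Conclusion.** The contradiction is certain on the text: the same examiners are described as blinded and as impossible to blind. It affects both primary outcomes, because the 9-month examination that yields them has no consistent statement on blinding.

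Two stronger conclusions are tempting. One is that outcome assessment is in fact unblinded; the documents show only that blinding is not assured. The other is that the bias would favour non-inferiority. An examiner who expects equal arms could pull the result that way, but one who favours or distrusts photography could push it either way, so the sign is unknown.

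The size is also unknown. The 1 point per 1% of children is arithmetic on an assumed net change confined to one arm. The documents give no rate of changed calls, and the 1% to 5% range is not an estimate.

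**What to change.** Reconcile the Allocation, Visual dental examination and Follow up sections as follows.

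1. State that OHTs who perform the 9-month examination are not told the school's allocation and, where existing staffing allows, did not chart images for that school.
2. Require tooth scores to be recorded before any enquiry about treatment received or adherence.
3. Have the examiner record whether they became aware of the allocation.
4. Limit the statement in Allocation about who cannot be blinded to participants, parents and any OHTs who deliver arm-specific results.
5. Study status says data collection is under way. For follow-up visits already completed, document and report the blinding actually achieved.

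The cost is revised wording, a fixed order of recording and minor scheduling constraints. The article mentions 2–4 charters but gives no number of operators, so separating charters from examiners at each school is conditional on staffing.

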#### Photographic dental assessment

As per dental screening protocol used in previous trials [26, 27], tele-assistants (trained research assistants) will acquire still dental images from children using a novel image acquisition App installed in smartphone devices (Fig. 1). The tele-assistants will be provided with a dental photography protocol and will receive hands-on training on how to use the image acquisition App and capture good images. Disposable cheek retractors will be used to assist in viewing teeth during dental photography. Using the mobile App, the tele-assistants will first create a basic registration (includes a unique ID, age in years, gender and school name) for each participant. Then a minimum of five still dental images per child will be taken (front, right lateral, left lateral, upper occlusal, and lower occlusal views). Following the completion of dental photography and creating a record on the App, each participant’s set of data (including dental images and anonymous patient details) will be then directly uploaded from the mobile App to a secure drive located at the CSIRO, for later evaluation by charters (Fig. 4). The assessment of dental images will be performed independently by 2–4 registered OHTs (charters). Charters will receive instructions on how to log in and use the web-based application (Remote-I), review images and insert findings back to the system. After selecting a record from the database, a list of dental images and a predefined assessment chart appears for the charter to insert their findings. The chart includes a digital oral health assessment form, which aligns with the WHO protocol for oral health assessments [35]. The system enables charters to independently review dental images and submit reports or treatment plans to the Remote-I system (Fig. 2). The assessment of dental caries will be completed at the tooth level rather than the tooth surface, based on a protocol developed by the WHO [35]. A copy of the screening results will be mailed to the parents of children in the teledental group that includes advice on the pathway of dental care or OHP material based on the assessment of dental images .

**Fig. 4 Fig4:**
[figure not shown]
Main workflow of the teledental screening process

#### Follow up

At 9 months following the baseline dental assessments, all participants will be invited to undergo a standard visual dental check-up to assess the dental status, determine if treatment was received and see whether parents adhere to the recommendations received at the baseline.

### Process evaluation

Regular auditing for OHTs will be conducted by an independent researcher to assess the intervention fidelity and determine whether the study protocol was followed as intended. Tele-assistants collecting dental images and OHTs participated in the charting of dental images will be surveyed to explore their acceptability of school dental screening based on dental photography.

To maximise retention of participants, all participants will receive a letter at the baseline on the importance of adhering to the intervention and on participation in the follow-up measurements as well as expected benefits including a free dental examination conducted within schools, and receiving screening report that includes preventive interventions to promote tooth brushing and healthy diet. To promote their active participation in the study, participants will receive Bright Smiles dental kits (consisting of toothbrush and toothpaste) at the end of the study.

### Outcome assessment

*Primary outcomes* include decay experience in either dentition as measured by the DFT/dft (decay, filled teeth) index at the baseline and 9-month follow up. Teeth will be classified as carious if have arrested caries, caries into dentine or enamel level caries. In addition to the proportion of children becomes caries-active at the 9-month follow-up which refers to the percentage of children developing one or more new caries in any of the previously caries-free teeth when assessed at the baseline. Data will be collected from one of our system’s functional components running on the backend to automatically record dental assessments based on dental images and through the oral health assessment forms completed by OHTs in the control group.

*Secondary outcomes* include the diagnostic performance of photographic dental assessment versus standard dental examination at the baseline. The participants’ dental care utilisation patterns collected via a baseline survey (Additional file 2) and adapted from Kopycka-Kedzierawski et al. [36]. Also, costs comparison between the two pathways of dental care will be conducted to identify the least costly alternative. The resources for the usual pathway of dental care will include vehicle costs, admin costs (e.g. telephone appointments, printing services and postage) and costs of consumables used in visual dental screening and the dental practitioner’s time. The resources for the teledental pathway of dental care include: software licence fees, ICT equipment, Internet and software engineer’s time, admin costs (e.g. telephone appointments, printing services and postage), costs of consumables used in dental photography, tele-assistants (photographer) time, and offsite dental practitioners’ time for reviewing dental images. Dental care costs for all children include the following: restorations, restorations with crowns and extractions. The costing data will be based on those incurred by the health system and will be derived from a survey and web-based open-access sources [37].

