### Data analysis

The sensitivity and specificity values for the photographic caries assessment will be estimated and compared to the reference visual dental assessment at the baseline. Kappa statistic will be used to estimate the inter-rater reliability of the photographic dental assessments by two independent OHTs. 15% of dental images will be re-examined to test intra-rater reliability at least, 4 weeks after the initial review of images.

The baseline data will be used to generate descriptive statistics for the intervention and control groups (teledental versus usual care pathway). General linear regression models will be performed to compare the efficacy of the interventions on decay (mean DFT/dft) between intervention and control groups, adjusting for baseline data collected via a survey that includes tooth brushing (yes/no; frequency); dental visit patterns over the past year, child age, Indigenous status, Socio-Economic Indexes for Areas (SEIFA), private insurance status and educational level of parents. The measure of intervention efficacy will be the difference between the intervention and control groups in adjusted DFT/dft (caries incidence) per child. All analyses will be performed using SAS (version 9.4). In addition, a cost minimisation analysis will be undertaken to compare the costs associated with teledental versus the usual pathway of dental care over 9 months. This will include both the cost of the initial screening, and any subsequent interventions occurring over the 9 months. The analysis will be conducted from the perspective of the health system and, will not take into consideration the costs incurred by the families. All salaries used in the calculation will be based on Australian government rates and will include on-costs.

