## Abbreviations

AEHRC: Australian e-Health Research Centre
CSIRO: Commonwealth Scientific and Industrial Research Organisation
DFT/dft: Count of decayed and filled teeth
ICT: Information and communication technology
OHP: Oral health promotion
OHT: Oral health therapist
SDS: School dental service
SEIFA: Socio-Economic Indexes for Areas
WA: Western Australia
WHO: World Health Organization

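### Neither primary outcome registers baseline decay that is missed and left untreated, and the DFT/dft difference is a net count, not caries incidence

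*Protocol article*

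**What the plan says.** The protocol article (Outcome assessment) gives two primary outcomes. The first is "decay experience in either dentition as measured by the DFT/dft (decay, filled teeth) index at the baseline and 9-month follow up"; the Abbreviations spell the index out as "DFT/dft: Count of decayed and filled teeth". The second is the "percentage of children developing one or more new caries in any of the previously caries-free teeth when assessed at the baseline".

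Three scoring rules matter here. On what counts as decay: "Teeth will be classified as carious if have arrested caries, caries into dentine or enamel level caries". On the unit, the section on photographic assessment says: "The assessment of dental caries will be completed at the tooth level rather than the tooth surface". And the index has no missing-teeth component, although the Background quotes national figures on an index that has one.

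Data analysis defines efficacy as the between-group difference "in adjusted DFT/dft (caries incidence) per child". The listed covariates are survey items; baseline DFT/dft is not among them.

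The arms differ in whether parents get results and advice from the visual examination or from photographs. In the control arm, "children with active caries will be referred to local dental providers for further investigations". The treatment expected to follow appears in the costing: "Dental care costs for all children include the following: restorations, restorations with crowns and extractions".

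**The concern.** The intervention changes how decay is found and, through that, whether it is referred and treated. The Background describes photographic screening as moderately accurate against visual screening. The foreseeable way for the teledental pathway to be worse is that a decayed tooth is missed on the images, not referred, and still decayed 9 months later. An outcome that scores that tooth the same as a filled one cannot separate the arms on it.

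The trial is a non-inferiority trial, so a contrast pulled toward zero favours the conclusion that the new pathway is no worse. The economic analysis is a cost minimisation, which makes sense only if the outcomes are comparable, so it inherits the same weakness.

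Separately, a count that falls when teeth are extracted or shed is a net quantity. Calling its difference caries incidence invites a misreading: the change in a child's count can be negative, and a fall need not mean better oral health.

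**Working it through.** **The plan's own figure.** Sample size calculation: 1.96² × 0.9 × 0.1 / 0.1² = 34.57, rounded up to 35 children with caries; 35 × 1.86 = 65 without; 100 / 0.80 = 125 per group. This reproduces. It rests on a single expected proportion of 0.90, not on DFT/dft, so it says nothing about the sensitivity of the primary index. It does supply the 35% prevalence used below.

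**Step 1: score each fate of one tooth found decayed at the baseline visual examination.**

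| Fate at 9 months | DFT/dft | Caries-active outcome | Untreated D/d |
|---|---|---|---|
| Found and filled | 1 | not counted | 0 |
| Missed and left decayed | 1 | not counted | 1 |
| Extracted | 0 | not counted | 0 |
| Shed | 0 | not counted | 0 |

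Only the last column separates the first two rows. A tooth sound at baseline that becomes decayed adds 1 to DFT/dft and makes the child caries-active, so new disease is registered by both primary outcomes.

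**Step 2: illustrate the size.** From the plan: prevalence 0.35. Assumed: k decayed teeth per affected child, visual sensitivity 1.0, photographic sensitivity s, every detected tooth filled, no new lesions. Decayed teeth per child: b = 0.35 × k. Difference in untreated decay (teledental minus control): b × (1.0 − s). Difference in DFT/dft: 0, because decayed-to-filled leaves the sum unchanged.

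| k | b | s = 0.9 | s = 0.7 | DFT/dft difference |
|---|---|---|---|---|
| 1 | 0.35 | 0.35 × 0.1 = 0.035 | 0.35 × 0.3 = 0.105 | 0 |
| 3 | 1.05 | 1.05 × 0.1 = 0.105 | 1.05 × 0.3 = 0.315 | 0 |

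**Step 3: allow extractions and incomplete uptake.** Assume k = 2 (b = 0.70), a share u = 0.8 of detected teeth treated, and a share e = 0.2 of treated teeth extracted. Untreated-decay difference: b × u × (1 − s). DFT/dft difference: b × u × e × (1 − s).

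- s = 0.9: untreated 0.70 × 0.8 × 0.1 = 0.056; DFT/dft 0.056 × 0.2 = 0.011.
- s = 0.6: untreated 0.70 × 0.8 × 0.4 = 0.224; DFT/dft 0.224 × 0.2 = 0.045.

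The DFT/dft difference is now positive, against teledental, because more teeth leave the count in the control arm. It carries only the share e of the untreated-decay difference, and only because the missing component is omitted.

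**The case against.** A reader might infer that DFT/dft cannot show any harm from missed referrals and is biased toward success throughout. The documents do not support that, for these reasons.

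- Both primary outcomes still count new lesions, and enamel lesions that reverse after advice would lower DFT/dft. The blindness concerns existing decay left untreated.
- Extraction does not push one way. If photographs miss decay, the control arm has more teeth extracted and teledental looks worse (Step 3). The direction depends on which arm has more extractions.
- Shedding happens in both arms and child age is a covariate. No reason is given why it should differ by arm, so it is mainly noise.
- Outcome assessment can be read as taking teledental data from the images and control data from the therapists' forms. If that fixed the baseline, a tooth missed on photographs would enter as sound and be found decayed at 9 months. A change score and the caries-active outcome would then count it against teledental. The 9-month mean would be unaffected.
- The failure is partly seen elsewhere. Baseline sensitivity against the visual reference is a secondary outcome, the 9-month visit asks whether treatment was received, and the Abstract says all children are first examined to identify urgent referrals.
- Separate reporting of components and rules for shed teeth may stand in a full protocol or SAP that is not shown.

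These points narrow the concern without removing it. Sensitivity measures detection, not whether the tooth was later treated. Treatment receipt is collected but not named as an outcome. The utilisation outcome comes from a baseline survey. The urgent-referral step does not cover non-urgent decay. The choice of index, the scope of the second outcome and the incidence label are stated in the article itself.

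**Conclusion.** The point holds in this limited form. By the plan's own definitions, neither primary outcome registers decay present at the baseline visual examination that is missed and left untreated. For those teeth the DFT/dft contrast is pulled toward zero, which favours non-inferiority. The adjusted DFT/dft difference is a net count and should not be called caries incidence.

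The documents do not allow the net bias of the whole comparison to be stated, and none is claimed. The illustrated gap in untreated decay, about 0.04 to 0.32 teeth per child against 0 in DFT/dft, rests on assumed tooth counts, sensitivities and treatment. Only the 35% prevalence comes from the plan. The 0.9 column matches the planning proportion if that is read as sensitivity; 0.7 is an assumption. The scoring result in Step 1 needs none of these assumptions.

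**What to change.** 1. In Outcome assessment, add as a key secondary outcome, compared between arms, untreated decay (D+d) at 9 months among teeth decayed at the baseline visual examination. Take it from the visual charts at both visits in both arms, and say so. Report D/d and F/f separately beside DFT/dft.
2. In Data analysis, either drop the incidence label or derive a tooth-level increment: teeth sound at the baseline visual examination that are decayed, filled or extracted for caries at 9 months, excluding exfoliated teeth. Tabulate extractions of baseline-decayed teeth separately.

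The new outcome should stay secondary: no margin or power has been worked out for it, and Study status says data are already being collected.

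Cost: some extra derivation, since every child is to be examined visually at baseline and invited back for a visual check at 9 months. One item may be new: the reason a tooth is absent at the 9-month visit, where not already known. For teeth whose reason stays unknown, report the increment with and without them.
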